### Outcomes

#### Primary outcome

Absolute and relative difference in the recruitment numbers of the observed studies before and after the intervention, in relation to the actual recruitment time. The primary outcome is the number of participants recruited per trial and week standardized by the targeted number of participants per week and the expected recruitment duration of the specific trial (actual recruitment number in week *i*/expected recruitment number per week, where expected recruitment number per week = target number of cases/duration of the trial in weeks and *i*=1, ..., observation period in week *i*, *j*=trial 1, ...,5, *k*=site 1, ...,10).

To account for site-specific and seasonal effects, a mixed model will be used.

#### Secondary outcomes

The absolute numbers ofPatients identifiedPatients incorrectly identifiedPatients recruited

per time-period, site, and trial, and contrasted for control and intervention phases.

 Determination of the usability, usefulness, and efficacy of the recruitment support.

#### Time schedule

*Recruitment*: Trials are included starting on June 1, 2021.

*Randomization*: At least one month prior to the inclusion of *a specific* trial into the study, the length of the control phase for this trial is randomized centrally across all 10 sites.

#### Sample size calculation

Sample size calculation is based on the assumption of a simple parallel group design. On a significance level of 5% and a power of 80%, an effect size of *d*=0.57 can be demonstrated with a two-sided *t*-test in a balanced design with a total number of 100 trials (10 per site). Even if this effect can be classified as strong, the dynamic Interrupted Time Series design offers more statistical power than a two-group t-test, especially when the number of data points is relatively large and the effect size is not small, as is expected in our case. This added power in the ITS design is mainly due to its methodology as it incorporates the temporal ordering of observations, which allows it to account for time-related effects. Thus, it can potentially provide a more accurate estimate of the intervention effect, especially when considering various variability factors (time, location). In addition, we aim to include as many trials as possible, potentially exceeding the total number of 100.

To assess the feasibility of this number, we searched ClinicalTrials.gov for trials registered and actively recruiting that began recruitment on 01-01-2021 or earlier and whose primary completion date is 01-01-2023 or later. Table 1 shows the results per site.

**Table 1 Tab1:** Number of recruiting trials at the participating sites with a start date on or before 01-01-2021 and primary completion on or after 01-01-2023 with the location filter set to the city name of the site

Site	Number of trials on ClinicalTrials.gov satisfying criteria for feasibility estimation
University Hospital Dresden	185
University Hospital Erlangen	214
University Hospital Frankfurt	189
University Hospital Freiburg	103
University Hospital Gießen	73
University Hospital Greifswald	29
University Hospital Magdeburg	58
University Hospital Mainz	116
University Hospital Mannheim	75
University Hospital Marburg	66

### Recruitment

To identify large and viable trials for the study, central and site-local trial registries are searched and trial personnel are contacted directly to contribute additional trials. To increase the sample size of the study, any eligible trial can be dynamically included in the study and allocated to a randomized time slot, generated prior to the start of the trial.

### Generation and implementation of allocation

Prior to the inclusion of *a specific* trial into the study, the length of the control phase for this trial is randomized centrally across all 10 sites. The overall observation period of the trials varies between 6 and 15 months. With a pseudo-random generator from the R-statistical package, the length of the control phase is randomly assigned to a value between 15% and 85% of the total observation period, which ensures that for short (6 months) trials control or intervention phases have at least a duration of one month. Respectively, a trial with an observation time of 15 months has control or intervention phases with a minimum length of 2.5 months. For each trial, an exact date for the start of the intervention phase is calculated from the inclusion date of the trial and the duration of the control phase.

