### Study design

The study uses an Interrupted Time Series (ITS) Design [21, 22] with a duration of 15 months. All trials start in the control phase of randomized length with regular recruitment and change to the intervention phase with additional IT support, ensuring a minimum of one month in each phase and a minimum trial observation of 6 months. At least one month prior to the inclusion of *a* specific trial into the study, the length of the control phase for this trial is randomized centrally across all 10 sites. A block randomization was used to randomize the time of switching to the new scheme in the percentage of the planned enrollment time into the study. We used R version 4.1.2 and the package blockrand version 1.5 with the seed 9384902. We allowed for values between 0.15 and 0.85 with 0.05 steps, rounding the resulting time of switching to the first or 15th of a month. We generated 5 blocks with a size of 30 resulting in 150 ids. When a study was enrolled at one of the sites, the site contacted the independent person at Freiburg, who took the next free id from the randomization list and relayed the time of switching for the specific study. The persons responsible for enrollment had no access to the randomization list.

Due to the embedding of the intervention into and its overlap with the recruitment processes, it is practically not feasible to completely blind the study. Nevertheless, the randomized time point to switch to the intervention will only be disclosed to the sites 2 months before and only subsequently to the medical staff. The effectiveness will be measured by the number of recruited participants per trial and week standardized by the targeted number of participants to be recruited into the specific trial. This will be analyzed by means of a linear mixed model. In addition, user interviews will be conducted prior to the start of the intervention and at the end of the study. 

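### The 15%–85% switch range does not ensure the stated minimum phases: before rounding the shortest phase is 0.9 month in a 6-month trial and 2.25 months in a 15-month trial

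*Protocol article*

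**What the plan says.** Under Generation and implementation of allocation, the protocol article says that "the length of the control phase is randomly assigned to a value between 15% and 85% of the total observation period". It credits the minimum phase lengths to this range: "which ensures that for short (6 months) trials control or intervention phases have at least a duration of one month", and "a trial with an observation time of 15 months has control or intervention phases with a minimum length of 2.5 months". The same section gives the span of observation: "The overall observation period of the trials varies between 6 and 15 months".

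Study design repeats the one-month property for the design as a whole, "ensuring a minimum of one month in each phase and a minimum trial observation of 6 months", and describes how the list was made: "We allowed for values between 0.15 and 0.85 with 0.05 steps, rounding the resulting time of switching to the first or 15th of a month". The two end values are therefore among those drawn. Neither section says whether rounding goes up, down or to the nearest date, limits the day of the month on which a trial may be included, or describes a check of the phase lengths once the date has been rounded. The allocation section does not mention rounding at all.

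**The concern.** A phase of at least one month in a 6-month trial needs a fraction of at least 1/6, or 16.7%. The range starts at 15%, so its extreme values miss a minimum that the protocol says they secure. The 15-month figure misses in the same way. Rounding the switch date could repair the shortfall or enlarge it.

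Two things are at stake. First, a design property stated in two sections is not delivered by the allocation rule. The outcome is counted weekly, so a phase well under a month adds very few points to that trial's before-and-after contrast. Second, Statistical methods expects no protocol deviations and says that trials are otherwise left out of the primary analysis. A trial that switches exactly as assigned could still fall below the stated minimum, and the text does not say how such a trial is to be regarded.

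**Working it through.** **Inputs.** Fractions 0.15 to 0.85 in steps of 0.05, which gives 15 values, and rounding to the 1st or 15th (Study design). Observation *T* of 6 to 15 months; stated minima of 1 month for *T* = 6 and 2.5 months for *T* = 15 (Generation and implementation of allocation). Assumption: one month = 30.4375 days.

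**Step 1: the stated minima, before rounding.** Minimum control phase = 0.15 × *T*. Minimum intervention phase = *T* − 0.85 × *T*.

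| *T* | Minimum control | Minimum intervention | Stated | Shortfall |
|---|---|---|---|---|
| 6 months | 0.15 × 6 = 0.90 | 6 − 5.10 = 0.90 | 1 | 0.10 month, about 3 days |
| 15 months | 0.15 × 15 = 2.25 | 15 − 12.75 = 2.25 | 2.5 | 0.25 month, about 7 to 8 days |

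In days: 0.90 × 30.4375 = 27.4 and 2.25 × 30.4375 = 68.5. Neither stated figure is reproduced.

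**Step 2: which bound would give them.** 1/6 = 0.167 and 2.5/15 = 0.167. Both figures match a range of 16.7% to 83.3%.

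**Step 3: which trials are affected before rounding.** 0.15 × *T* < 1 gives *T* < 1/0.15 = 6.7 months. The next fraction gives 0.20 × 6 = 1.2 months, so only 0.15 and 0.85 fall short. That is 2 of 15 values, or 13% of draws for a 6-month trial.

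**Step 4: rounding in a 6-month trial.** All 15 fractions were enumerated for trials of 182 to 183 days, with inclusion dates over one year from June 1, 2021. Rounding direction and inclusion day are assumptions, because the protocol gives neither.

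| Rounding | Inclusion day | Shortest phase |
|---|---|---|
| None | any | 27 days |
| Nearest 1st or 15th | 1st or 15th only | 28 days |
| Nearest 1st or 15th | any | 19 days |
| Always up, or always down | any | 11 days |

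With nearest rounding and any inclusion day, about 9% to 10% of allocations in such a trial leave a phase under 30 days. A few of these come from 0.20 and 0.80, so rounding also reaches draws that met the minimum beforehand.

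**Step 5: rounding in a 15-month trial.** On a half-month grid, 2.25 and 12.75 lie midway between grid points.

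- Halves rounded up: 2.5 months of control, but a switch at 13.0, which leaves 15 − 13.0 = 2.0 months of intervention.
- Halves rounded to even: 2.0 months in each phase.
- Rounded down: 2.0 months of control and 15 − 12.5 = 2.5 months of intervention.

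None of the rules tried gives 2.5 months in both phases.

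**The case against.** **Rounding may restore the month.** If trials enter only on the 1st or 15th and the switch goes to the nearest such date, 0.9 month becomes 1.0 and 5.1 becomes 5.0. The shortest phase is then 28 days, and counted in calendar months the control phase was never short in that enumeration. This stands as a favourable case. But the protocol does not require those conditions, it credits the minima to the percentage range rather than to rounding, and the 2.5-month figure is not rescued.

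**The one-month minimum may be a separate constraint.** The Study design sentence can be read that way. No step that would enforce it is described.

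**The effect is slight.** This stands. The primary analysis is a mixed model on weekly data pooled over about 100 trials. No separate baseline fit per trial is described, and a 27-day phase still yields nearly four weekly points. The protocol does not say how many trials have observation under 6.7 months, so 13% and 9% to 10% describe a 6-month trial and are not study-wide rates.

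**A reader might infer that short-phase trials are excluded from the primary analysis.** The document does not support this. Statistical methods does not define a short phase as a deviation, and a trial that switches on its centrally assigned date has followed the procedure.

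**Conclusion.** The two minima are wrong as written. Before rounding, the range gives 0.90 month in a 6-month trial and 2.25 months in a 15-month trial. These results need only the protocol's own figures. After rounding, the 6-month minimum lies between about 11 and 28 days, and this range rests on the assumed rounding direction and inclusion days.

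No effect on bias, type I error or power is shown, and the sample size does not use the phase lengths. Loss of trials from the primary analysis is not a consequence that can be claimed; the most that can be said is that the status of a short assigned phase is left open. This is an inconsistency that is cheap to correct, not a flaw that undermines the design.

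**What to change.** 1. In Generation and implementation of allocation, give the minima as 0.9 month (6-month trial) and 2.25 months (15-month trial) before rounding, and bring the one-month statement in Study design into line.
2. State the rounding rule, including its direction and whether inclusion is limited to certain days of the month.
3. For allocations still to be made, if the one-month minimum is to be kept: where a rounded date leaves a phase under one month, move it to the nearest 1st or 15th that leaves at least one month in each phase. This fixed rule should be applied by the independent person who holds the list.
4. For trials already allocated, report the true minimum phase length, and state under Statistical methods that a short phase resulting from the assigned switch date is not a protocol deviation.

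The cost is a few sentences and one date check per new allocation, which pulls some extreme switch dates slightly inward. Narrowing the range for short trials is not advised: the list is a single sequence of 150 ids in 5 blocks of 30, already generated and used in order whatever the trial's length, and a second range would disturb it.

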### Blinding

Due to the embedding of the intervention into and its overlap with the recruitment processes, it is practically not possible to completely blind the study. Nevertheless, the randomized time point to switch to the intervention will only be disclosed to the site’s medical staff 1 month before. The randomization list is generated prior to the start of the evaluation study by an independent statistician and kept secret.

### Data collection

The following data is collected for each trial:

Trial specific parametersParticipating sitesRegistration information: unique trial identifier such as the ClinicalTrials.gov NCT number, the DRKS number, or the Universal Trial Number (UTN)Start of recruitmentPlanned and actual end of recruitmentExpected duration of recruitmentTargeted participant countExpected number of participants at each siteNumber of participants already recruited at the beginning of the studyTrial typeInclusion criteriaExclusion criteriaPersons (or groups) involved in recruitmentNumber of patients who were admitted to the site on a monthly basis as in- or outpatients

During the intervention:Number of screenings conductedNumber of recruited participants per weekNumber of recruitment proposals per week (automatically recorded by the IT-solution)Number of recruited participants not suggested by the system per week (i.e., only through standard recruitment procedures)

After the intervention:

Short interviews and surveys on the usability of the system are conducted with one user for each trial. To quantify the user experience and usability of the tool, the System Usability Scale (SUS) [25] and the User Experience Questionnaire - short (UEQ-S) [26] will be used.

Per recruitment proposal:

The following data is collected for each recruitment proposal. A suitable feedback mechanism for reporting trial inclusions must be established individually at the centers.Organizational unit of the site where the inclusion took place (automatically recorded by the IT system)Status as indicated in the recruitment list.“Recruitment Proposal”“Under consideration”“Does not meet eligibility criteria”“Is Participating in trial”“Not willing to participate”Outpatient or inpatient status at the time of inclusion

The patient inclusion data is primarily collected via the trial’s existing electronic documentation and transferred to custom data entry masks. To ensure the completeness of data collection, the documentarians from MIRACUM are in close exchange with the corresponding staff in the departments and trial personnel.

### Data management

REDCap is used as a data acquisition tool.

Data on individual patients (the minimal amount of data needed to present patients as screening recommendations) are stored pseudonymized, in accordance with the local data protection regulations.

### Statistical methods

The characteristics of the included studies will be presented in tabular form. All variables will be summarized using appropriate summary statistics. The mean, standard deviation, and the quantiles will be used for continuous variables and absolute and relative frequencies for categorical variables. If applicable, the variables will be visualized using boxplots and histograms, potentially over time.

The primary analysis will be conducted using linear mixed models with the actual recruitment number per week and trial standardized by the expected recruitment number per week and trial as the dependent variable. The choice is driven by the model’s ability to account both for fixed effects and random effects. This flexibility of this model is particularly suited for capturing the hierarchical structure in our data and aligns with the nature of the ITS design, where repeated measures over time and within-trial correlations are essential. A positive and statistically significant fixed effect of the binary variable “intervention allocation per week” will be interpreted as the measure for effectiveness. The corresponding effect will be evaluated for significance on the 5% level using the likelihood-ratio test. The model will be adjusted for trial, site, season, and time via random effects. Primarily, compound symmetry is considered as a working covariance matrix (constant correlation between time points), while autoregressive and unstructured covariance matrices are used as sensitive analysis. Additional sensitive analysis involves larger time frames, i.e., per month instead of per week, other distributions and link functions, i.e., generalized models, and classical statistics via mean values. Given the conservative sample size calculation based on a *t*-test, the linear mixed model is backed with adequate statistical power given the expected heterogeneous nature of the data.

To uncover further correlations and generate hypotheses, explorative analysis is carried out, including specific evaluation of site and trial characteristics.

No deviations from the protocol or missing data are expected. Trials are otherwise excluded from the primary analysis and their characteristics are compared to the other trials to identify potential problems for generalizability of the results.

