### Intervention

The intervention consists of the application of a complex recruitment-support system, which should be utilized alongside the standard recruitment procedure. Patient data, which is already collected in the context of general care, will be used for screening according to trial-specific criteria. The de-identified patient data, located in the data integration centers of the sites, are continuously compared against inclusion and exclusion criteria of clinical trials. This requires first translating the necessary eligibility criteria of all selected trials into a machine-readable format. The recruitment support system uses the OMOP common data model [18] to store patient data which includes OHDSI ATLAS as a tool for defining patient cohorts. ATLAS is a user interface where researchers can graphically define a cohort using a set of logical expressions that are internally converted to SQL to be executed against the database. This tool is used to identify and translate the eligibility criteria collaboratively with the trial personnel [23, 24]. During the intervention phase, all patient data is regularly checked against the defined cohorts. When eligible patients are detected, the staff is informed about the proposals by email, and the de-identified data is presented on a web-based screening list. The dataflow is shown in Fig. 2.

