**Fig. 2 Fig2:**
[figure not shown]
The basic flow of data from the electronic health records (EHRs) to the research repositories to the creation of patient recommendations in the screening list. Treatment data is recorded in the EHR as part of routine care (1), this data is regularly transformed to the OMOP CDM via ETL jobs (2). A query module (3) continuously scans the research repository for patients matching the defined trial eligibility criteria. If potential candidates are found, they are put on a web-based screening list (4), and a notification is sent via email. This notification is received by relevant practitioners or trial personnel (5) and the screening list can be accessed to further manually screen the suggested patients

Local recruitment staff decides over inclusion of individual patients based on the recruitment proposals on the screening list. Patient status, from recruitment proposal to inclusion, is documented in the screening list. Because it is based on pseudonymized research data, by default, this list displays only a pseudonymized medical record number, the year of birth, the gender, and the last known organizational unit within the hospital. This data can be used to either search the hospital information system with its applicable access controls, or the study personnel has to contact the attending physician based on the last known location of the patient. After consenting to disclose trial and personal data, the staff can then inform the patient about a possible participation in the trial. Some sites allow displaying the re-identified medical record number to make it easier to identify the patient. In these cases, re-identification works by technically integrating the screening list with the pseudonymization tooling established at the sites.

In the control phase, trial participants are recruited according to the respective standard procedure.

Termination criteria are not defined, since the interventional IT solution is used parallel to the conventional solution.

To increase the adherence of the recruiting staff, training courses are conducted and regular visits take place. Problems with adherence are logged.

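### The primary effect is a single step from the first intervention week, so a start-up delay would attenuate it and a start-up burst could pass for a sustained gain

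*Protocol article*

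**What the plan says.** Under Statistical methods, the dependent variable is weekly recruitment per trial divided by the expected weekly number. One binary weekly variable carries the intervention effect: "A positive and statistically significant fixed effect of the binary variable" for intervention allocation "will be interpreted as the measure for effectiveness", and the test is fixed: "The corresponding effect will be evaluated for significance on the 5% level using the likelihood-ratio test". On adjustment: "The model will be adjusted for trial, site, season, and time via random effects".

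The sensitivity analyses cover autoregressive and unstructured covariance, monthly data, generalized models and comparisons of means: "Additional sensitive analysis involves larger time frames, i.e., per month instead of per week, other distributions and link functions". None of them changes the immediate, constant step.

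The Intervention section describes how a proposal becomes an inclusion. "During the intervention phase, all patient data is regularly checked against the defined cohorts". Staff are then notified by email and screen the list by hand. They find the patient through the hospital information system, or "the study personnel has to contact the attending physician based on the last known location of the patient". Only after that is the patient informed and possibly included.

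Under Generation and implementation of allocation, the switch falls between 15% and 85% of an observation period of 6 to 15 months, so that in short trials "control or intervention phases have at least a duration of one month".

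**The concern.** The outcome is counted at the end of a chain of steps, but the indicator switches on at its start. Two departures from a constant step are plausible.

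- **Delay.** Inclusions in the first intervention weeks may still come from patients identified under the control procedure. The step then averages weeks without an effect and weeks with one, and shrinks.
- **Burst.** If the first query returns a stock of existing matches, early weeks may show a one-off rise. The step is then positive even if nothing remains afterwards.

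One coefficient cannot separate these patterns from a constant effect. At stake are the power to detect a useful tool and the reading of a positive result as a continuing gain. The issue weighs more here because intervention phases can be as short as about a month.

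**Working it through.** **1. The plan's own figure.** Sample size calculation: 100 trials, 50 against 50, two-sided 5%, 80% power, d = 0.57. A two-sample t-test gives a detectable d of 0.566, and power of 80.6% at d = 0.57. The figure is reproduced. It treats the effect as fully present throughout the intervention phase.

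**2. Phase lengths.** Switch fractions from 0.15 to 0.85 in steps of 0.05 give 15 values (Study design). With T weeks observed, the intervention phase is m = T × (1 − fraction).
- 6 months (T = 26): m runs from 3.9 to 22.1 weeks with mean 13. The four latest switches leave 7.8, 6.5, 5.2 and 3.9 weeks. The first 4 weeks are about 4/13 = 31% of intervention time.
- 15 months (T = 65): m runs from 9.75 to 55.25 weeks.

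Rounding the switch to the first or 15th of a month moves these figures slightly.

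**3. Hand check without time adjustment.** With trial effects only, each trial has weight m(T − m)/T, and a delay of L weeks leaves the share 1 − L/m of the effect in its intervention mean. Where L does not exceed the shortest phase, the pooled share is

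kept = 1 − L × mean(T − m) / mean[m(T − m)].

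Over the 15 switch values, mean(T − m) = 0.5T and mean[m(T − m)] = 0.2033T², so kept = 1 − 2.46 × L/T. For L = 4:
- T = 65: 1 − 2.46 × 4/65 = 0.85.
- T = 26: 1 − 2.46 × 4/26 = 0.62. The 3.9-week phase is a negligible exception to the formula.

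**4. Closer to the stated model.** Setup: 100 trials, staggered entry, random trial intercepts (variance 0.2 of residual) and random calendar-week intercepts (variance 0.0001 to 0.2 of residual). These variances are assumptions. Share of a delayed effect kept by the step coefficient:

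| Assumed delay | Mixed 26-65 weeks | All 6 months | All 15 months |
|---|---|---|---|
| 2 weeks | 80-90% | 76-82% | 83-93% |
| 4 weeks | 61-79% | 54-64% | 68-85% |
| 8 weeks | 31-60% | 24-36% | 40-71% |

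With random calendar months in place of weeks, the mixed-length ranges are 78-89%, 58-79% and 26-59%, and the 4-week range for 6-month trials extends down to about 49%. Stronger time adjustment lowers the share, because it gives more weight to weeks near the switch.

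**5. Burst.** A burst of L weeks is the full step minus the step delayed by L weeks. The estimator is linear, so its coefficient is 1 − kept. At 4 weeks with mixed lengths this is 1 − 0.79 = 0.21 to 1 − 0.58 = 0.42 of the burst height, although the later effect is zero.

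**6. Power on the plan's own approximation.** Power ≈ Φ(d × kept × √(50/2) − 1.96), using the mixed-length shares with almost no time adjustment:
- no delay: Φ(0.57 × 5 − 1.96) = Φ(0.89) = 81%
- 2 weeks (0.90 kept): Φ(0.605) = 73%
- 4 weeks (0.79 kept): Φ(0.29) = 61%
- 8 weeks (0.59 kept): Φ(−0.28) = 39%

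**7. With a separate start-up indicator.** If the window matches the true start-up length, the established-use coefficient recovers 100% of a delayed effect and 0% of a pure burst.

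**The case against.** The strongest reply is that the objective and outcome concern numbers recruited before and after the switch. An average over all intervention weeks is a legitimate answer to that. Backlog recruits are real participants, slow starts are a real cost, and the protocol nowhere promises a steady-state effect. This stands, and it is the reason to keep the all-weeks step as primary.

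A reader might infer more than the documents support:

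- **That an ordinary delay hides most of the effect.** No delay is stated. Under random time effects with mixed lengths, 2 to 4 weeks costs a minority of the effect. Losing most of it takes about 8 weeks, and for mixed or 15-month trials even that depends on the time variance. Much larger losses appear only with fully fixed time effects, which is not the stated model.
- **That the start-up period routinely fills the intervention phase.** At 4 weeks this applies only to a 6-month trial switching at 85%, one of 15 switch values.
- **That the study could not detect a transient at all.** Weekly proposals, weekly recruits and recruits not suggested by the system are collected, and plots over time and exploratory analyses are foreseen. A burst could show there, but not in the coefficient that decides effectiveness.
- **That the coding produces false positives.** With no effect in any week, a delay changes nothing.

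Delay and burst also act in opposite directions, so the net bias has no known sign. An analysis plan that is not shown may add a lag analysis. The article itself, however, fixes the coding, the decision rule and a list of alternatives, none of which relaxes the step.

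**Conclusion.** The point holds as a limit on what the primary coefficient can show. If start-up takes several weeks, the estimate is attenuated: moderately for mixed lengths (about 58-79% kept at 4 weeks) and substantially if all trials are short (about 49-64%). If start-up brings a burst, a positive coefficient can reflect a transient. The direction of each bias follows from the coding. The size rests on assumed delay or burst lengths, assumed variance ratios and assumed trial lengths, none of which the documents give. It is not an error that invalidates the primary test.

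**What to change.** Keep the randomized switch and the all-weeks step as primary. Pre-specify a companion analysis in the same mixed model with two indicators in place of one: the first 4 weeks after each switch (transition), and all later intervention weeks (established use). Vary the window, for example 2 and 8 weeks, or use a term for time since the switch, because a 4-week window corrects a longer delay only in part. Report both coefficients beside the primary one. Claim a sustained gain only if the established-use coefficient supports it. State how the window relates to the one-month minimum phase.

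The switch dates and weekly counts that the primary analysis already needs are sufficient, so the change is one of wording. With a 4-week window and mixed lengths, the standard error of the established-use coefficient is about 6-13% larger than that of the all-weeks step. A 6-month trial switching at 85% contributes control and transition weeks only.
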